### Physical activity and sedentary behaviour (accelerometry) mediating and exposure variables

Participants will be asked to wear an ActiGraph GT3X or a GT3XP-BTLE accelerometer on the right hip for seven consecutive days to measure physical activity (ie, light, moderate and vigorous) and sedentary (eg, amount of time spent sitting) behaviour. Following wear, the raw accelerometry data will be downloaded, screened, cleaned and processed using ActiLife 6 Software (ActiGraph, Pensacola, Florida, USA). Accelerometer data will be collected at 100 Hz, and processed data will be stored as ‘activity counts’ per 15 s epochs. The activity intensity of each 15 s epoch will be classified using the Copeland & Esliger cut points (sedentary behaviour ≤99, light physical activity 100–1040 and moderate-to vigorous physical activity ≥1040).^41^ To be included, a participant needs at least 3–5 days of at least 8–10 hours of wear time. Non-wear is defined as a period of 120 min.^42^ The data will be scored, and specific cut-points will be applied as follows: sedentary behaviour ≤99; light physical activity 100–1040 and moderate-to vigorous physical activity ≥1040.^41^

Derived physical activity variables from accelerometry will include:

Average acceleration (activity counts).Average acceleration per day.Average acceleration per weekday.Average acceleration per weekend day.The most active part of the day.Average acceleration in the most active hours.The least active part of the day.Average acceleration in the least active hours.Time spent in sedentary behaviour.Time spent in light physical activity.Time spent in moderate physical activity.Time spent in vigorous physical activity.

### GPS

Participants will also be asked to wear a GPS device (Qstarz BT-Q1000XT) concurrently with the accelerometer for seven consecutive days (the exact placement of the GPS device (eg, right, or left hip) does not influence the recording). The GPS device is a ‘black box’ monitor that uses GPS technology to record the location of participants. Although the data are recorded in real time, the collected data cannot be accessed by the research team until the participant returns the device, therefore preserving anonymity of real time location. The GPS monitor will provide an x.y coordinate for every 15 s. This allows physical activity data from the accelerometer to be accompanied by locational information by matching the timestamps from each device. Although we will have access to the x.y coordinates of participants movements, and therefore an understanding of home and neighbourhood locations, data will be analysed by assigning each x.y coordinate of the participant home address a land use category (eg, home, parcel, greenspace) and subsequently converted into variables that represent the total time spent in specific land use. GPS data will be downloaded using QTravel software.

### GIS, accelerometry and GPS data integration—exposure through behaviour

We will use the Human Activity Behaviour Identification tool and data Unification System (HABITUS) to process and integrate the accelerometer, GIS, and GPS data.^43^Available as an R package,^44^ HABITUS streamlines the data processing in four other existing tools (GGIR, ActivityCounts, PALMSpy and palmsplusr). Figure 1 shows the data integration process through these tools. HABITUS also ensures autocalibration and imputation of missing data for accelerometer and GPS recordings. As both the accelerometer and GPS devices were set to record every 15 s, this enables the physical activity behaviour data from the accelerometer to be linked to the environmental location data (ie, x.y coordinates) from the GPS device by timestamp. These integrated data will be merged using an ‘exposure through behaviour’ method, which has been outlined elsewhere.^45^ In brief, the timestamps from both the accelerometer and GPS data will be matched, so that time spent in every physical activity intensity (ie, sedentary behaviour and light, moderate and vigorous physical activity) or travel mode (ie, active or passive), in every pre-determined space (eg, home, parcel, local neighbourhood and green and blue space) via GIS analysis can be calculated. See figure 3 for schematic diagram of data integration.

**Figure 3 F3:**
[figure not shown]
Data integration process using HABITUS. GIS, Geographic Information System; GPS, Global Positioning System; HABITUS, Human Activity Behaviour Identification tool and data Unification System.

Derived variables following data integration via HABITUS will include:

Time spent in/out home, parcel, neighbourhood (500 m and 1000 m).Time spent in green and blue spaces.Time spent in non-domestic properties (eg, shops, offices, warehouses, licensed premises, sporting recreation, community centres).Time spent in urban or rural areas.Time spent near or on road networks.Time spent in different levels of air, noise, light pollution.Time spent in different transportation modes (active and passive).

Additionally, we will select a subset of GPS coordinates that belong to trips outside of the home location. Using this subset, we will identify a minimum convex hull, a polygon enclosing all points, for each participant. This polygon will then be used to define each participant’s ‘activity space’ and overlay this polygon with corresponding GIS data to derive additional variables.^46^

Derived variables based on activity spaces will include:

Average exposure to air pollution outdoors.Average exposure to noise pollution.Average exposure to light pollution at night.Visits to non-domestic properties (eg, shops, offices, warehouses, licensed premises, sporting recreation, community centres).

#### Molecular mediating data

Blood-derived biochemical data is available for 28 markers for 3082 participants within the NICOLA cohort (see online supplemental table 1). Blood-derived biochemical, genetic and epigenetic data will be combined with demographic, clinical, behavioural and environmental data for multimodal analyses. DNA was extracted from buffy coats by Eurofins Scientific, quantified using PicoGreen, normalised and aliquoted into multiple working volumes in cryvials to minimise freeze-thaw cycles and maximise the quality of DNA. Genotype data was generated on the Infinium CoreExome-24 array (Illumina, USA), with standard quality control applied and imputation to the 1KGP3, HRC and TopMed reference panels. Kinship matrices have been generated. Association analysis will be performed, but the primary utility of genetic data is to enable Mendelian Randomisation to explore causal inference and to help interpret epigenetic findings. DNA methylation is the primary molecular ‘ome’ of interest for this study, due to its ability to dynamically changes in response to medical, lifestyle and environmental changes. Methylation data were generated using Infinium MethylationEPIC 1.0 BeadChips (Illumina, USA) after bisulphite treatment with the EX Zymo Methylation Kit (Zymo Research, USA) following manufacturer’s instructions. Participant samples were randomly distributed across 249 arrays, with quality control including eight duplicate samples (n=16) and evaluation of the bisulphite treatment conversion efficiency, dye specificity, hybridisation and staining. Samples were initially assessed using GenomeStudio v2011 and the BeadArray Controls Reporter software platforms (Illumina, USA). Crossreactive probes, those located within 3 bp of common SNPs, and those on sex chromosomes will be excluded from primary analyses. Unreliable probes and samples will be removed before association analysis is performed. Proportional white cell counts will be estimated for CD8+T, CD4+T and CD19+B lymphocytes, CD56+ natural killer (NK) cells, CD14+ monocytes and CD15+ granulocytes using the Houseman method.^47^ Beta values were generated before M values were derived for all sites. P values were computed using the limma method for each site.^48^ Hierarchical linear models from the limma package were employed and fitted using Bayes approach on the derived M values. P values were generated for each of the four differential analyses conducted. RnBeads will be used to perform EWAS with single site resolution with multivariate regression analysis performed for quantitative traits adjusting for sex and age. RNA was collected in Paxgene tubes and extracted by Eurofins with quantitation performed on a Bioanalyser. Samples with a RIN >6 underwent sequencing using either a whole transcription or AmpliSeq technology for library preparation on an Ion Chef and subsequent sequencing on an Ion Proton or Ion GeneStudio S5 system (Life Technologies, USA). Transcriptome-wide association analysis will be performed, but the primary utility of this dataset for this project is to help understand the functional impact of epigenetic changes. Individual ‘omic’ analyses, exploring contributions from individual omics as well as a combined model, will be conducted with Mendelian Randomisation employed to explore causal influences with a composite multimodal biomarker signature generated. This project will provide more knowledge on the mechanistic pathways underlying how the urban environmental exposome affects cognitive outcomes in older adults, identify which environmental impact has the most biological impact, and has potential to identify a multiomic signature for people at higher risk of cognitive decline.

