### Confounders

Confounders such as age, sex, education, employment status, smoking, diet, cardiovascular risk factors, depression, years at home address will be accounted for.

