Multivariate analysis of variance will be conducted to investigate the difference in participant compositions (ie, part 1a and 2a) and the outcome of cognitive health. Compositional data analysis which is based on isometric log-ratio data transformation will then be conducted to model the association of time spent in different movement behaviours during waking hours and cognitive health.^64 65^ Minute-by-minute isotemporal substitutions will be made from one behaviour to another while holding the remaining behaviours constant, to model change in cognitive health. Adjustments for potential confounders and mediators will be made and includes age, sex, socioeconomic status, lifestyle behaviours (eg, smoking, drinking), disability, car ownership etc.

To control for multiple comparisons, the false discovery rate correction will be applied using the Benjamini-Hochberg procedure, adjusting for the total number of analyses conducted.

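### The EWAS is stated as adjusting for sex and age, while the estimated white-cell proportions enter no model and smoking is not tied to it, so its associations may be confounded

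*Protocol article*

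**What the plan says.** All references are to the Protocol article.

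- **Molecular mediating data, EWAS model.** The single-site analysis in RnBeads is specified as "multivariate regression analysis performed for quantitative traits adjusting for sex and age". The limma analyses described just before it are given without any covariates.
- **Molecular mediating data, source of DNA.** "DNA was extracted from buffy coats by Eurofins Scientific".
- **Molecular mediating data, cell proportions.** "Proportional white cell counts will be estimated for CD8+T, CD4+T and CD19+B lymphocytes", then for natural killer cells, and for "CD14+ monocytes and CD15+ granulocytes using the Houseman method". That makes six cell types. The article does not say where these estimates are used.
- **Confounders.** "Confounders such as age, sex, education, employment status, smoking, diet, cardiovascular risk factors, depression, years at home address will be accounted for". The sentence names no model and does not mention cell mix.
- **Compositional data analysis.** Smoking is named for this analysis, within "lifestyle behaviours (eg, smoking, drinking), disability, car ownership etc".

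Methylation is the molecular layer the study puts first, on the ground that it responds to lifestyle and environment, among other things.

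**The concern.** Buffy-coat DNA carries a mixture of methylation profiles, one for each leucocyte type. If a trait such as activity, pollution exposure or cognition is related to the mix of cells, methylation at cell-type-specific sites will be associated with that trait even when nothing has changed within any cell. Smoking can act in the same way if it relates both to the trait and to methylation. A model with sex and age alone does not block either path.

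The article itself supplies the reasons to expect more covariates: it plans the cell estimates and it counts smoking as a confounder. The section goes on to a combined omic model, Mendelian randomisation and a composite biomarker signature, and aims to rank environmental influences by biological impact. A cell-mix or smoking signal could be read there as mechanism.

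**Working it through.** **No figure to reproduce.** The article gives no alpha, power, effect size or sample size for the EWAS. The check is therefore a comparison of passages, followed by an illustration under stated assumptions.

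**Passages side by side**

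| Factor | Named in the EWAS model | Elsewhere in the article |
|---|---|---|
| Age, sex | Yes | Confounders; Compositional data analysis |
| Six cell proportions | No | Estimated in the same section; no use stated |
| Smoking | No | Confounders (no model named); Compositional data analysis |
| Array | No | Samples allocated to the 249 arrays at random |

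**Illustration.** Let trait X and methylation site M have no direct link, and let both correlate with an omitted factor C (cell mix or smoking).

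- Without C in the model: corr(X,M) = r_XC × r_CM. With C measured without error it is 0.
- Rejection probability (Fisher z, two covariates): d = atanh(r) × √(n − 3 − 2), and P = Φ(d − z) + Φ(−z − d).
- Inputs: n=400 is the study's anticipated uptake (Sample size section). n=3082 is the number with biochemical markers and serves only as an illustrative upper value, because the methylation n is not given. r_XC, r_CM and a site threshold of 10⁻⁷ (z about 5.33) are assumptions.

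Worked case: r_XC=0.2, r_CM=0.5, n=400. Then r=0.10 and d = 0.1003 × √395 = 1.99. P is 0.514 at z=1.96 and 4.3 × 10⁻⁴ at z=5.33.

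| n | r_XC | r_CM | P at 0.05 | P at 10⁻⁷ |
|---|---|---|---|---|
| 400 | 0.05 | 0.3 | 0.060 | 2.6 × 10⁻⁷ |
| 400 | 0.05 | 0.7 | 0.107 | 1.8 × 10⁻⁶ |
| 400 | 0.1 | 0.3 | 0.092 | 1.1 × 10⁻⁶ |
| 400 | 0.2 | 0.5 | 0.514 | 4.3 × 10⁻⁴ |
| 400 | 0.3 | 0.7 | 0.989 | 0.14 |
| 3082 | 0.05 | 0.3 | 0.132 | 3.5 × 10⁻⁶ |
| 3082 | 0.1 | 0.3 | 0.384 | 1.3 × 10⁻⁴ |
| 3082 | 0.2 | 0.5 | 1.000 | 0.59 |
| 3082 | 0.3 | 0.7 | 1.000 | about 1.0 |

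**Second parameterisation.** Take r_XC=0.15 and 30% of a site's variance due to cell mix. The non-centrality is 0.15 × √0.30 × √400 = 1.64. A null site then reaches p<0.05 with probability 0.376, and passes 10⁻⁷ with probability about 1.2 × 10⁻⁴, roughly 1,000 times nominal. With r_XC=0.05 instead, the rate at 0.05 is about 8.5%.

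**After adjustment.** With C in the model and measured without error, the rate returns to nominal. Estimated proportions and imperfectly recorded smoking would leave some residual confounding.

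**The case against.** The strongest reply is that this is wording, not a decision. The article does not say that sex and age are the only covariates. The Confounders section is general and could be read to cover smoking in the EWAS. Estimating cell proportions suggests an intention to adjust for them, and a condensed article may leave the full covariate list to another document.

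Part of this stands: the text is inconsistent, and a reader should not infer a deliberate choice to exclude these factors. It does not remove the point. A covariate set is stated, it is narrower than the general sentence, and nothing anywhere puts cell mix into a model. A detail left to a fuller plan is one thing; a stated set that disagrees with the rest of the article is another.

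Four further objections stand and limit the claim:

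- **Yardstick.** An EWAS does not select sites at p<0.05, so the 0.376 above is not a rate of false hits. It also applies only to sites with the assumed share of variance from cell mix, and the proportion of such sites is unknown. The false discovery rate correction appears at the end of the Compositional data analysis section and may or may not reach the EWAS. In either case it does not remove confounding.
- **Arrays.** It is tempting to add batch confounding over 249 arrays. Random allocation means array is not expected to confound.
- **Downstream use.** A reader might infer that EWAS-selected sites enter the mediation models. The article does not say so; the bootstrap mediation test under Mediation analysis concerns lifestyle behaviours. The EWAS sentence speaks of quantitative traits and does not specify exposure-methylation models.
- **Pathway.** The Introduction says activity reduces inflammatory markers. If exposure alters leucocyte mix through inflammation, cell mix lies partly on the pathway of interest, and adjustment alone could hide a real effect.

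**Conclusion.** The point holds as an inconsistency with analytic consequences. Following the stated EWAS model leaves cell mix and smoking uncontrolled, so trait-methylation associations may be confounded. The inflation ranges from minor (6% against 5% at r_XC=0.05, r_CM=0.3, n=400) to large (0.14 against 10⁻⁷ at r_XC=0.3, r_CM=0.7, n=400), and it grows with sample size because the bias does not shrink.

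These figures rest on assumed correlations and an assumed site threshold. A reader might go further and infer that most EWAS hits will reflect cell mix or smoking. The documents do not support that, since they give neither the correlations nor the methylation sample size. The correction should be made before the EWAS is run.

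**What to change.** In the Molecular mediating data section:

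1. State the EWAS covariates as age, sex, the estimated cell proportions with one type omitted (they sum to about one), smoking, and the other factors in the Confounders section that apply to the trait; or give the reason for leaving any of these out.
2. Report genomic inflation for each EWAS.
3. Present results with and without the cell-proportion terms, because cell mix may partly mediate exposure effects.
4. Treat array terms as optional, for precision only. Do not enter array as 249 fixed levels: that would use up to 248 degrees of freedom, which is prohibitive near n=400.

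The cost is a few degrees of freedom (five for six cell types with one omitted, plus smoking and any other confounders entered) and one extra model run. The cell proportions are already planned and smoking is already a listed confounder.

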
#### Cognitive health outcome variables (HCAP)

Cognitive health will be assessed by the HCAP, which comprises 19 measures of cognitive health which after following written informed consent will be conducted by a trained researcher in the participant’s home (table 2).^27^

**Table 2 T2:** HCAP measures of cognitive health^26 27^

Outcome measure	Cognitive domain
Mini-Mental State Examination (MMSE)	Global cognitive status
HRS Telephone Interview for Cognitive Status (HRS-TICS)	Global cognitive status
CERAD Word List Learning and Recall—Immediate	Episodic memory (immediate)
Retrieval fluency (Animal naming)	Language/fluency
Letter cancellation	Attention/processing speed
Backward count	Attention/processing speed
10/66 Respondent	Global cognitive status
CERAD Word List Recall—Delayed	Episodic memory (delayed)
Story recall—Immediate	Episodic memory (immediate)
CERAD Word List—Recognition	Episodic memory (recognition)
CERAD Constructional Praxis—Immediate	Visuospatial ability
Symbol-Digit Modalities Test	Attention/processing speed
CERAD Constructional Praxis—Delayed	Visual memory (delayed)
Story recall—Delayed	Episodic memory (delayed)
Story recall—Recognition	Episodic memory (recognition)
HRS Number Series	Executive function
Raven’s Standard Progressive Matrices	Abstract reasoning
Trail Making Test (Part A & B)	Executive function/attention/processing speed
CES-D Depressive Symptoms	Assessment of presence and level of depression

Tests listed in order of administration. Psychological Assessment Resources (PAR), [name], from the Mini Mental State Examination, by Marshal Folstein and Susan Folstein, Copyright 1975, 1998, 2001 by Mini Mental LLC. Published 2001 by PAR. [[contact]].

CERAD, Consortium to Establish a Registry for Alzheimer’s Disease; CES-D, Centre for Epidemiological Studies Depression Scale; HRS, Health and Retirement Study.

NICOLA-HCAP also includes an informant interview whereby the participant is asked to nominate a family member or friend to answer questions about their daily activities and cognitive abilities over time (table 3). The interview includes family or friend demographics and the following six measures:

**Table 3 T3:** HCAP informant interview measures^26 27^

Outcome measure	Description
Family or friend demographics	Demographic profile of informant
Jorm IQCODE	Assessment of cognitive decline
Blessed dementia rating scale—Part 2	Assessment of ability to do basic self-care activities
HRS Activities questionnaire	Assessment of participant activity engagement
CSI-D—Cognitive Activities Questionnaire	Assessment of participant’s cognitive activity engagement and ability
10/66 Informant Questionnaire	Assessment of ability to do daily activities
Blessed dementia rating scale—Part 1	Assessment of additional activities and mental ability

Tests listed in order of administration.

CSI-D, Community Screening Instrument for Dementia; HRS, Health and Retirement study; IQCODE, Informant Questionnaire on Cognitive Decline in the Elderly.

Following data collection and processing, domain-level factor scores derived from the scores on the cognitive battery will be used in conjunction with informant measures to develop algorithm-based research diagnoses of probable dementia or cognitive impairment. This approach has previously been used to estimate dementia prevalence in the HRS-HCAP substudy.^49^ In a supplementary analysis, we will retrofit this predicted algorithmic score to the full Wave 1 and Wave 2 NICOLA longitudinal dataset.

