### Study population

For the purposes of the current study, we leverage the Northern Ireland Cohort for the Longitudinal Study of Ageing (NICOLA) and the NICOLA Harmonised Cognitive Assessment Protocol (HCAP) substudy (NICOLA-HCAP).^24^,^27^ NICOLA is a prospective representative cohort of over 8000 non-institutionalised individuals living across Northern Ireland, UK ≥50 years of age.^24 25^ Wave 1 of the NICOLA-HCAP study recruits a subsample of 1000 participants from NICOLA aged ≥65 years who previously took part in Wave 2 of NICOLA.^27^ The NICOLA-HCAP study is part of a framework for enhancing cross-national research within a group of ongoing studies worldwide, all of which are centred on the United States-based Health and Retirement (HRS) international family of longitudinal ageing cohort studies.^26 28^

The NICOLA-HCAP protocol consists of a battery of neuropsychological tests and is designed to provide detailed data on ability across a range of cognitive domains, including memory, executive function, language and visuospatial ability. The protocol was originally developed and implemented within HRS and has since been implemented in several other national ageing cohorts.^28^,^31^ The protocol is designed to be delivered in a harmonised way across studies to facilitate cross-national comparisons of dementia prevalence and risk factors. For the first wave of this study, we will recruit a sub-sample of participants from NICOLA-HCAP.

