#### Sample size

The NICOLA-HCAP assessment will be offered to the NICOLA participants aged ≥65 years, with a random sample of 50% of those living alone (n=1695) and a random sample of 50% of those living in a partnership or with a sibling etc. (n=2401). The response rate for the NICOLA-HCAP is expected to be approximately 80% and assuming a selection rate of ~1 in 3 to achieve the target of 1000 participants. Of 1000 NICOLA-HCAP participants, there is an anticipated uptake to the current study of ~40% (n=400).

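### The impairment score is derived at age 65 and over but retrofitted to a cohort recruited from age 50, with no age limit stated

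*Protocol article*

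**What the plan says.** The derivation is described in the section on cognitive health outcome variables (HCAP): "domain-level factor scores derived from the scores on the cognitive battery will be used in conjunction with informant measures" to produce research diagnoses of probable dementia or cognitive impairment. The informant element belongs to the substudy: "NICOLA-HCAP also includes an informant interview whereby the participant is asked to nominate a family member or friend". Under Study population, the first wave of that substudy "recruits a subsample of 1000 participants from NICOLA aged ≥65 years who previously took part in Wave 2 of NICOLA".

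The application follows in the same outcome section and is labelled supplementary: "we will retrofit this predicted algorithmic score to the full Wave 1 and Wave 2 NICOLA longitudinal dataset". The parent cohort is wider than the substudy: "NICOLA is a prospective representative cohort of over 8000 non-institutionalised individuals living across Northern Ireland, UK ≥50 years of age".

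The mediation section says that cognition was measured in NICOLA Waves 1 and 2 but does not list the tests. The article states no age restriction on the retrofit. It also does not give the age distribution of NICOLA, the number seen at Wave 2, or the dates of Waves 1 and 2.

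**The concern.** The stated target of the score is wider than the population in which it is derived, in three respects.

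- **Age.** No one aged 50-64 contributes to the derivation, so nothing in the derivation data supports the score there. Prevalence of impairment and test performance both vary with age, and a rule tuned at 65 and over may classify differently below that age.
- **Selection.** HCAP members must have taken part in NICOLA Wave 2. People seen at Wave 1 who died or left before Wave 2 or HCAP are in the target data but cannot be in the derivation data. This affects scores at 65 and over as well.
- **Inputs.** The classification uses HCAP domain scores and informant measures. The article does not show that either exists in Waves 1 and 2. If they do not, the algorithm cannot be applied as defined, and a model with fewer inputs has to stand in for it at every age.

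At stake is age-dependent misclassification in the retrofitted scores, and in any change from Wave 1 to Wave 2 computed from them.

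**Working it through.** **Step 1: compare the two populations.**

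| | Derivation | Application |
|---|---|---|
| Population | NICOLA-HCAP | Full NICOLA Waves 1 and 2 |
| Age | 65 or over | 50 or over |
| Size | 1000 | Over 8000 in the cohort |
| Entry condition | Took part in NICOLA Wave 2 | None beyond the cohort |
| Inputs | HCAP domain scores and informant measures | Cognition measured; tests not listed |

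The age gap follows directly from the stated scope and needs no arithmetic.

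**Step 2: find what the sample-size counts mean.** For one stratum, the Sample size section gives "a random sample of 50% of those living alone (n=1695". The other stratum, people who share a household, is worded the same way with a count of 2401. It is unclear whether the counts are the strata or the 50% samples. Their sum is 1695 + 2401 = 4096. The section expects 80% response and selection of about 1 in 3 to reach 1000.

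- 4096 as the pool, 1 in 3 selected: 4096 × 1/3 × 0.80 = 1092. This is 9% above 1000. Exactly 1000 needs 1 in 4096 × 0.80 / 1000 = 3.28, which is compatible with about 1 in 3.
- 4096 as the pool, 50% selected: 4096 × 0.5 × 0.80 = 1638.
- 2048 as the pool, 50% selected: 2048 × 0.5 × 0.80 = 819.

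Taking 4096 as everyone aged 65 or over fits best, but the wording does not settle it.

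**Step 3: share of NICOLA under 65.** Share = 1 − (number aged 65 or over) / N. The article says only that N is over 8000; the range up to 8900 is an assumption.

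| N | 4096 is the whole pool aged 65+ | 4096 is the 50% sample, so 8192 aged 65+ |
|---|---|---|
| 8000 | 1 − 4096/8000 = 48.8% | 1 − 8192/8000 = −2.4% (impossible) |
| 8200 | 50.0% | 0.1% |
| 8500 | 51.8% | 3.6% |
| 8900 | 54.0% | 8.0% |

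The second reading sits badly with a cohort recruited from age 50, but it is closer to the literal wording.

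**Step 4: other unknowns.**

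- If 4096 counts only Wave 2 participants, and 70-90% of 8000 were retained (assumption), the share under 65 at Wave 2 is 1 − 4096/5600 = 27% to 1 − 4096/7200 = 43%.
- Participants were younger at Waves 1 and 2 than at the HCAP offer, which raises the share. With an assumed gap of 2 to 8 years and ages uniform over 65-85 or 65-90, the first reading at N = 8000 gives about 53-69%.
- Older people who died or left before HCAP may be missing from the 4096, which lowers the true share by an unknown amount.

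These unknowns pull in opposite directions, and the article gives nothing to resolve them.

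**The case against.** The best defence is that this is one sentence, about a supplementary analysis, in a condensed article. The score is called predicted, which may already mean a model of the HCAP classification on items shared with Waves 1 and 2, where cognition was measured. The predictor list, validation and handling of prediction error usually sit in a fuller document. None of the three planned analyses in the statistical section names this score, and the total-effect outcome is the MMSE.

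Most of that stands. The absence of modelling detail is not itself a fault, and a mismatch of tests between HCAP and Waves 1 and 2 cannot be demonstrated, because the Wave 1 and 2 tests are not listed. What does not fall away is the scope. The article says the full dataset, and that dataset belongs to a cohort aged 50 or over. This is a stated choice rather than an omitted detail, and a shared-item model fitted at 65 and over would still extrapolate below that age.

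A reader might go further and infer that about half or more of the scores are extrapolated, or that at most 51% of the cohort lies in range. The counts are too ambiguous for either, and the 51% (4096/8000) is not a ceiling once losses before HCAP are considered. A reader might also infer that the score will be treated as an observed endpoint, driven by age-type predictors, with standard errors that ignore prediction error. The article states none of this: it names no age predictor, no model using the retrofitted score and no variance method.

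**Conclusion.** The concern holds in a limited form. The score is derived at age 65 and over and applied, without an age limit, to a cohort aged 50 and over. Every score at ages 50-64 is therefore an extrapolation in age. The share cannot be established from the article: possibly about half if 4096 is the whole pool aged 65 or over, and far less if it is the 50% sample. Separately, the article does not show that the algorithm's defining inputs were collected in Waves 1 and 2. That leaves a question over all retrofitted scores, not a demonstrated fault.

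Severity is minor. The analysis is supplementary and bears on neither recruitment, sample size, the MMSE outcome nor any of the listed models.

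**What to change.** - Restrict the supplementary retrofit to person-waves aged 65 or over, or report ages 50-64 separately and label them as extrapolated.
- State that the retrofit uses only items recorded both in HCAP respondents and in NICOLA Waves 1 and 2, and name them. If the informant measures are not among them, say so.
- Report cross-validated discrimination and calibration of that model in HCAP respondents.
- Carry the result as a predicted probability rather than a diagnosis.
- Clarify whether 1695 and 2401 are strata or sampled halves, and give the number of person-waves under 65, so that readers can judge the extent of extrapolation.

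The cost is some extra analysis and, if ages are restricted, a smaller supplementary sample with wider intervals. No new data are needed.
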